# The EMPOWER-SUSTAIN e-Health Intervention to improve patient activation and self-management behaviours among individuals with Metabolic Syndrome in primary care: study protocol for a pilot randomised controlled trial

**DOI:** 10.1186/s13063-020-04237-x

**Published:** 2020-04-05

**Keywords:** E-health intervention, Self-management, Patient activation, Chronic Care Model, Chronic disease management, Multifaceted intervention, Metabolic syndrome, Primary care

## Abstract

**Background:**

Epidemiological studies conducted in various parts of the world have clearly demonstrated that metabolic syndrome (MetS) is an increasing global health problem, not only in Western societies but also in Asian populations. Web-based and mobile phone-based self-management applications have been proven to be effective in improving self-management behaviour of patients with MetS components (i.e., diabetes or hypertension). However, evidence is lacking in terms of their effectiveness specifically for patients with MetS. The aim of this pilot study is to evaluate the feasibility and potential effectiveness of the EMPOWER-SUSTAIN Self-Management e-Health Intervention in improving activation and self-management behaviours among patients with MetS. This paper presents the study protocol.

**Methods:**

A pilot randomised controlled trial will be conducted in a university primary care clinic. A total of 232 patients aged 18–60 years with MetS will be recruited; 116 will be randomised to receive the EMPOWER-SUSTAIN intervention for 6 months, and another 116 patients will continue with usual care. The EMPOWER-SUSTAIN intervention is a multifaceted chronic disease management strategy based on the Chronic Care Model and persuasive technology theory. It consists of training primary care physicians, nurses and patients to use the EMPOWER-SUSTAIN web-based self-management mobile app, strengthening the patient–physician relationship and reinforcing the use of relevant clinical practice guidelines to guide management and prescribing. The primary outcome is the mean change in patient activation score using the Patient Activation Measure short form Malay version (PAM-13-M) questionnaire. The secondary outcomes include the changes in waist circumference, body mass index, blood pressure, patient physical activity level, eating behaviour, perception of chronic illness care, satisfaction with patient–physician interaction, and perceived absolute 10-year cardiovascular disease risk. Feasibility of implementing the intervention will be evaluated. This includes acceptability of the intervention, estimating the likely rate of participant recruitment and retention, appropriateness of the outcome measures, calculation of sample size, and the intervention’s potential effectiveness.

**Conclusion:**

To our knowledge, this is the first study in Malaysia that aims to determine the feasibility of a multifaceted e-health intervention, as well as to indicate more useful aspects of this intervention for further exploration in a larger trial.

**Trial registration:**

ClinicalTrials.gov, NCT04120779. Registered on 9 October 2019, protocol version 1.

## Background

According to the International Diabetes Federation (IDF) consensus worldwide definition of metabolic syndrome (MetS), it is estimated that around 20–25% of the world’s adult population have MetS [1, 2]. The cardiovascular disease (CVD) risk factors tend to cluster in an individual, giving rise to MetS, which is defined by the presence of central obesity, elevated blood pressure (BP), elevated plasma glucose, and dyslipidaemia [3]. The prevalence of MetS ranges from 11.9% to 37.1% in the Asia-Pacific region, based on a systematic review [4]. These include the Philippines (11.9%), China (21.3%), Sri Lanka (24.3%), Taiwan (25.5%), Singapore (26.9%), South Korea (31.3%), Mongolia (32.8%) and Malaysia (37.1%) [4]. In Malaysian adults ≥30 years old, the prevalence of MetS was found to be 43.4% [5]. A recent review showed that MetS affected 25–44% of the adult population in Malaysia, with the risk increasing with age [6].

The prevalence of MetS has reached epidemic proportions in many Asian countries, including Malaysia, especially in the younger generations [7, 8]. Rapid economic growth, socio-demographic change, and adoption of unhealthy lifestyle that have all occurred over the past few decades are thought to be responsible for this rising prevalence [9]. This in turn has resulted in an upsurge of CVD morbidity and mortality in Malaysia [9]. A recent national report showed that among 95% of patients presenting with acute coronary syndrome (ACS), 46.2% had diabetes, 64% had hypertension and 38.6% had dyslipidaemia [10]. Malaysians were found to develop ACS at a younger age than their Asian and Western counterparts [10]. The mean age of individuals with ACS at admission in Malaysia was 58.6 years old, 23.6% of whom were under the age of 50 years [10].

One of the promising approaches to improve management of MetS in primary care is the integration of the Chronic Care Model (CCM) into the health system. The CCM is the best-known model for transforming chronic disease management in primary care [11]. It focuses on linking informed, activated patients with proactive and prepared health care teams [11, 12]. CCM offers effective strategies to improve chronic disease outcomes in primary care [12, 13]. A series of recent studies have indicated that CCM improves the quality of care and outcomes for patients with various chronic conditions [14–16]. In Malaysia, our previous work has shown that it was feasible to implement the CCM in the primary care setting [17]. In the EMPOWER-PAR Study, we have shown that the implementation of at least three components of CCM, which include self-management support and improved glycaemic control among patients with type 2 diabetes mellitus [18].

One of the most essential components of the CCM is self-management support, which encompasses activities that empower patients to become activated to manage their own health [11, 12]. International clinical guidelines recommend the inclusion of self-management programs in the management of MetS and the associated cardiovascular (CV) risk factors, and such programs have been associated with improved health outcomes [12, 19]. A systematic review of 19 studies reveals that self-management intervention improved outcomes, including haemoglobin A1c (HbA1c), waist circumference (WC), self-efficacy and empowerment in patients with MetS [20]. Lifestyle modification intervention has been shown to be effective in improving fasting blood glucose (FBG), WC, BP and triglycerides (TG) in patients with MetS [21].

Conceptually, self-management has a close association with patient activation and empowerment [22, 23]. Patient activation reflects patients’ central role in having the knowledge, skills and confidence to make effective decisions to self-manage their own health and change their behaviour (e.g., in adopting a healthy lifestyle) [23–26]. It is considered to be the most reliable indicator of the willingness and ability to manage health autonomously [27–29]. Previous studies have emphasised that increased patient activation level has been shown to improve self-management behaviours, such as physical activity (PA), diet and medication adherence, in patients with various chronic conditions [25, 30–32]. Patient activation has also been shown to improve quality of life and health outcomes and to reduce the use of health care services and costs for patients with various chronic conditions [25, 30–33]. However, there is a gap in the literature pertaining to intervention targeting to improve patient activation in patients with multiple CVD risk factors, such as MetS, especially in the younger generations.

To meet the growing demands of the younger generation, efforts have been made to develop web or mobile applications for self-management of multiple CV risk factors [34–38]. To ensure sustainability, the application should be developed using an evidence-based approach such as persuasive technology [39]. This technology was established to motivate people by influencing attitudes and behaviours of the users through persuasion and social influence, but not through pressure or force [39].

However, to our knowledge, there is no e-health self-management system which has been developed to suit the younger generations with MetS in Malaysia. Therefore, the objective of this study is to evaluate the feasibility and potential effectiveness of the EMPOWER-SUSTAIN Self-Management e-Health Intervention (multifaceted strategies involving web-based self-management mobile apps based on the CCM and persuasive technology theory) in improving patient activation and self-management behaviours compared with usual care among individuals with MetS in the Malaysian primary care setting. This paper describes the design of the trial as well as the development of the EMPOWER-SUSTAIN Self-Management e-Health Intervention and its underpinning conceptual frameworks.

### Hypotheses

The primary hypothesis is that the mean score of patient activation would improve with the EMPOWER-SUSTAIN Self-Management e-Health Intervention. The secondary hypotheses are that WC, body mass index (BMI), BP, PA level, eating behaviour, patients’ perceptions and experiences of receiving care for chronic conditions, patient–physician satisfaction, and the accuracy of the CVD risk perception would improve with the EMPOWER-SUSTAIN Self-Management e-Health Intervention.

### Trial design

This is a pilot randomised controlled trial with parallel group design (i.e., intervention vs. control [usual care] with an allocation ratio of 1:1). The overall duration of the study is 1 year, and the duration of the intervention is 6 months. Blinding is not possible, owing to the nature and complexity of the intervention.

## Methods

### Protocol registration

The study protocol is registered with ClinicalTrials.gov (identifier NCT04120779), and the registration complied with all the items in the World Health Organisation Trial Registration Data Set. This is the first version of the study protocol. The reporting of this paper is done in accordance with the Standard Protocol Items: Recommendations for Interventional Trials (SPIRIT) 2013 guidance and checklist for protocols of clinical trials [40] and the Consolidated Standards of Reporting Trials (CONSORT) checklist for pilot and feasibility trials [41]. The SPIRIT checklist is provided in Additional file 1. Figure 1 shows the EMPOWER-SUSTAIN CONSORT flow diagram [41].

**Fig. 1 Fig1:**
[figure not shown]
The EMPOWER-SUSTAIN Consolidated Standards of Reporting Trials (CONSORT) flow diagram

### Study setting

This pilot study will be conducted at a university primary care clinic, which is located in the state of Selangor, Malaysia. It is a busy primary care clinic with a load of approximately 500 patients per day. Almost 70% of the patients are under regular follow-up at this clinic for various long-term conditions, including MetS.

The pilot randomised controlled trial [42] is conducted to ensure that the intervention can be delivered as intended and that safe assumptions can be made about effect size, rate of recruitment and retention in the future definitive clinical trial [43]. In this pilot study, the feasibility of implementing the EMPOWER-SUSTAIN Self-Management e-Health Intervention for patients with MetS in a primary care clinic will be evaluated. These include acceptability of the intervention, estimating the likely rate of participant recruitment and retention, appropriateness of the outcome measures, calculation of sample size, and its potential effectiveness (i.e., the effect size) [44, 45].

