### Monitoring the intervention

During the 6-month intervention period, patients are required to use the EMPOWER-SUSTAIN self-management mobile app for a cumulative period of 2 h and be seen at least once by the PCPs for follow-up care. A separate web interface will be created for PCPs to monitor patients’ log-in frequency and duration of use of the tool. Patients who do not comply with the use and follow-up requirements will be considered as lost to follow-up. Patients who are lost to follow-up or who withdraw from the trial will not be replaced. Analysis will be by intention to treat (ITT). There is no other specific concomitant care and intervention that are permitted or prohibited during the trial.

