### Primary outcome

The primary outcome will be measured by the mean change in patient activation score using the Patient Activation Measure short form–Malay version (PAM-13-M) questionnaire [24].

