### Feasibility outcomes

Process evaluation to assess the integrity of the randomised controlled trial protocol will be conducted. These include recruitment rate, methods of randomisation, retention rate, appropriateness of the primary and secondary outcome measures, sample size calculation, whether the intervention could be delivered as intended, and methods of statistical analysis to evaluate the potential effectiveness. Qualitative studies to explore facilitators and barriers in delivering the intervention among PCPs and using the intervention among patients will also be conducted. However, detailed methods for the qualitative studies are beyond the scope of this paper.

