## Discussion

To the best of our knowledge, the EMPOWER-SUSTAIN project is the first self-management e-health intervention designed for patients with MetS in the Malaysian primary care setting. The pilot randomised controlled trial will be conducted to evaluate the feasibility and potential effectiveness of the EMPOWER-SUSTAIN intervention, including recruitment rate, methods of randomisation, retention rate, selection of primary and secondary outcome measures, sample size calculation, whether the intervention could be delivered as intended, and methods of statistical analysis to evaluate the potential effectiveness [44, 45]. All of these aspects will be useful for further exploration in a larger definitive trial.

The EMPOWER-SUSTAIN Self-Management e-Health Intervention is expected to yield important new evidence on the potential improvements of patient activation and self-management behaviours among patients with MetS in a developing country. It is hypothesised that patients’ activation, WC, BMI, blood pressure, PA level, eating behaviour, perception and experience of receiving chronic disease care, patient–physician satisfaction, and perceived absolute 10-year CVD risk would improve with the EMPOWER-SUSTAIN Self-Management e-Health Intervention.

The EMPOWER-SUSTAIN intervention is a complex, multifaceted chronic disease management strategy based on three CCM elements (i.e., delivery system design, self-management support and decision support). It consists of training the PCPs, nurse, and patients to use the EMPOWER-SUSTAIN web-based self-management mobile app, strengthening patient–physician relationship, and reinforcing the use of relevant CPG for management and prescribing. This intervention is developed on the basis of MRC recommendations, guided by the best available evidence and appropriate framework [46, 47].

It is well established that the CCM is one of the best-known models to transform chronic disease care [11]. The EMPOWER-SUSTAIN intervention focuses on linking informed, activated patients with proactive and prepared practice team (i.e., PCPs and nurse) [11, 86]. The self-management mobile app is developed as a tool for health care providers to support and engage patients so that they are empowered with knowledge, skills and confidence to take independent actions to manage their own health [11, 12].

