## Conclusion

Ultimately, the results of this pilot study will determine the feasibility of this multifaceted e-health intervention, as well as indicate more useful aspects of this intervention for further exploration in a larger trial. This study will also provide evidence of potential effectiveness of a multifaceted intervention involving a web-based self-management mobile app, which is developed on the basis of CCM and persuasive technology theory in the primary care setting. It is hoped that the evidence derived from this study will provide a platform to support a larger definitive clinical trial to evaluate the effectiveness of this e-health self-management intervention in Malaysia.

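### The pilot's effect size is called a safe assumption for the definitive trial, but on the plan's own figures it is too imprecise to size one

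*Protocol article*

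**What the plan says.** The Study setting section gives the purpose of the pilot: to check that the intervention can be delivered as planned, and so that "safe assumptions can be made about effect size, rate of recruitment and retention in the future definitive clinical trial". The same section then names the feasibility outputs, among them "calculation of sample size, and its potential effectiveness (i.e., the effect size". The primary outcome is the "mean change in patient activation score using the Patient Activation Measure short form–Malay version (PAM-13-M) questionnaire", so the effect size that matters most for sizing is the PAM-13-M difference between arms.

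The Feasibility outcomes section says of the process evaluation: "These include recruitment rate, methods of randomisation, retention rate, appropriateness of the primary and secondary outcome measures, sample size calculation". It also includes delivery as intended and the methods of analysis. The Discussion adds that "All of these aspects will be useful for further exploration in a larger definitive trial". The Sample size determination section plans 97 per group for a difference of 3.93 with SD 9.70, raised to 116 per group (232 in total) for 20% drop-out.

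**The concern.** One sentence puts three quantities on the same footing, although the design does not estimate them equally well. A proportion such as retention, or an SD, is fixed fairly tightly by about 200 patients. A difference between two means is not, when the trial is sized to have only 80% power to detect it.

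Required sample size varies with the inverse square of the assumed difference, so a moderate error in the difference becomes a large error in the next trial's size. A pilot estimate that is high by chance would give a definitive trial that is too small; one that is low by chance would give a needlessly large trial or put the sponsor off running one. Since informing the definitive trial is a stated purpose of the pilot, the sentence misdescribes what the pilot can deliver.

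**Working it through.** **Inputs** (Sample size determination): difference 3.93 (5.97 − 2.04); SD 9.70; two-sided α 0.05; power 80%; ratio 1:1; 116 per group; 20% drop-out. Patients are treated as independent.

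**1. The plan's own figure.** n per group = 2 × (1.96 + 0.8416)² × SD² / d² = 15.70 × 94.09 / 15.44 = 95.6, so 96 by the normal approximation. The t-based solution is 96.6, so 97. The stated 97 is reproduced.

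**2. Precision of the pilot effect.** Completers: 116 × 0.8 = 92.8, so 93 per arm. SE = 9.70 × √(2/93) = 1.42.
- Normal: 3.93 ± 1.96 × 1.42 = 1.14 to 6.72.
- t with 184 df: 3.93 ± 1.973 × 1.42 = 1.12 to 6.74.

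The half-width is about 71% of the estimate.

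**3. What those limits imply for the next trial**, by the formula in step 1 with SD 9.70 (limits unrounded):

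| Assumed difference | Patients per arm |
|---|---|
| 1.14 (normal lower limit) | about 1,130 |
| 1.12 (t lower limit) | about 1,170 |
| 3.93 | 96 |
| 6.7 (upper limit) | 33 |

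This is roughly a 35-fold range. With no drop-out (116 per arm) the t interval is 1.42 to 6.44, or about 733 to 36 per arm.

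**4. Sizing on the observed value.** Suppose the true difference is 3.93, and the next trial is sized on whatever the pilot observes.
- One SE high (5.35): 52 per arm, about 54% power for the true difference.
- One SE low (2.51): 235 per arm, about 99% power.
- Simulation, if a trial follows only a significant pilot (93 per arm): mean observed difference about 4.45, which is 13% too high (4.45 / 3.93 = 1.13). Median power of the next trial is about 73%.

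**5. What the pilot estimates well.**
- SD: chi-square interval with 184 df around 9.70 is 8.80 to 10.80. At a fixed difference of 3.93 this gives 79 to 119 per arm.
- Overall retention of 80%: 1.96 × √(0.8 × 0.2 / 232) = 0.051, about ±5 points (Wilson 74.6% to 84.8%). In a single arm of 116 it is ±7.3 points. Retention here means having 6-month outcome data. The Monitoring the intervention section also counts as lost to follow-up those who miss the app-use or visit requirement, which is a different quantity.
- Recruitment rate: not computed, because the article gives no number to be approached.

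**6. Clustering.** Five physicians deliver the intervention. Correlation within physician could widen the interval in step 2, but the article gives no ICC, so no figure is attached.

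**The case against.** This is not a small pilot. With 93 per arm it has about 79% power for 3.93, and its interval is narrower than that of the source trial behind 3.93: about 0.45 to 7.41, taking 58 and 68 patients from the stated t-test degrees of freedom. It would also give an estimate in the target population with the Malay instrument. All of this stands, and it is why the PAM-13-M difference is worth reporting. It does not make the difference a safe assumption.

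The article never says that the definitive trial will be sized on the observed point estimate, and nobody proposes sizing at a confidence limit. That is also fair. The 33 to 1,170 range shows how little the estimate settles; it is not a forecast. The 54% power figure is one chosen scenario with a favourable mirror image, so the 13% inflation and median power of 73% are the less selective summary.

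A reader might infer that the decision to proceed would rest on the PAM-13-M effect. The documents do not support that: recruitment and retention stand in the same sentence as effect size, the Feasibility outcomes section adds process and qualitative work, and the Discussion says all aspects inform the larger trial.

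A reader might also infer that feasibility will be judged after the event, because no progression threshold appears although the Conclusion says that "the results of this pilot study will determine the feasibility of this multifaceted e-health intervention". But that is a closing summary, and the article condenses a full protocol that is not shown and may hold such criteria. Silence here is at most a question to the full protocol.

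**Conclusion.** The point holds for the effect size only. The Study setting section attributes to the pilot a property that its own planning figures rule out: an observed difference of 3.93 would be compatible with true differences from about 1.1 to 6.7. The SD and overall retention are precise enough to plan from, so the rest of the sentence's intent can be kept.

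The figures assume SD 9.70, 20% drop-out, an observed difference equal to the planned one, and independent patients. No drop-out narrows the interval only to 1.4–6.4. Using the source trial's control-arm SD of 10.01 widens it slightly, to 1.03–6.83 at 93 per arm.

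The consequence falls on the definitive trial. The conduct and primary analysis of this pilot are not affected.

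**What to change.** In the Study setting section:

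1. Remove effect size from the list of safe assumptions, leaving recruitment and retention.
2. State that the definitive trial will be sized on an important PAM-13-M difference set in advance, with the SD, recruitment and retention taken from the pilot.
3. State that the pilot's PAM-13-M difference will be reported with its 95% CI, as supportive evidence of potential effectiveness.

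Separately, ask the sponsor whether the full protocol holds progression criteria; no particular thresholds are proposed here.

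The cost is protocol wording. The downside is that the sponsor has to choose and justify an important difference beforehand. The Trial status section shows that recruitment had not begun when the article was written, so the change could have been made before any data were seen.
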